### Selection of Study Centers

All study centers are part of the German Inflammatory Bowel Disease (IBD) Study Group and are chosen according to their main area of focus and their experience in the treatment of UC. By signing the investigator agreement, each study center selected confirms its fulfilment of all formal requirements for inclusion in the study and guarantees its compliance with data privacy laws and any other regulations pertaining to the execution of this observational study.

### Participant Criteria

The inclusion criteria for the study include (1) clinically and endoscopically confirmed diagnosis of UC, (2) study-independent treatment with golimumab according to current medical practices, (3) age ≥18 years, (4) sufficient German language communication skills, (5) ability of the patient to understand the nature, significance, and scope of the clinical trial and make an independent decision based on this knowledge, and (6) elevated calprotectin levels (≥100 mg/L or ≥100 mg/kg) within 3 weeks prior to inclusion.

Our exclusion criteria include (1) infectious colitis, (2) off-label treatment with golimumab, or (3) treatment with golimumab within the previous 3 months.

### Study-Specific Interventions

No medical interventions are carried out in the course of the study other than those required by standard medical procedure. When taking routine blood samples, golimumab serum levels and ATG levels should also be monitored if possible. Only the natural progress of the disease in UC patients is monitored and evaluated.

### Schedule of Visits

There are no defined study visits. In the course of the study, the only clinical and laboratory data recorded are those corresponding to standard medical procedure. Data are recorded in the following observational weeks: baseline, 2, 6, 14, 22, and 26. Deviations of +/- 3 days from this documentation schedule fall within the scope of the study protocol. The period until the next examination is subsequently shortened or lengthened accordingly in order to compensate for deviations and maintain the examination rhythm.

The following data are recorded at the initial screening/baseline examination: date of consent, screening date, inclusion and exclusion criteria, personal information (date of birth, sex, height, weight), date of initial diagnosis, information regarding prior anti-TNFα medication, partial Mayo score, laboratory tests (hemoglobin, WBC, platelet, ferritin, CRP, fecal calprotectin, and ATG), and medication (dose of golimumab, cortisone, and azathioprine).

The following data are recorded during each subsequent examination (week 2, 6, 14, 22, and 26) in the course of the study: partial Mayo score, laboratory tests (hemoglobin, WBC, platelet, ferritin, CRP, and fecal calprotectin), and medication (dose of golimumab, cortisone, and azathioprine). In addition, in Weeks 2 and 6, golimumab trough serum levels and ATG are measured.

### Documentation

Data are recorded using case report forms (CRF). The investigator is responsible for the timely, correct, complete, and legible recording of study data in the CRF and confirms recording by signature. CRF are completed with a black ballpoint pen. Corrections are documented as follows. The wrong entry is crossed out with a single line, and corrections are entered next to the crossed-out text and verified by date and initials, stating the reason for the change if necessary. Instructions for use (entry and corrections) are included in each CRF. Source data according to the ICH E6 guideline on good clinical practice (GCP) are original documents in patient files, as well as doctors’ letters, certified copies of original records, and laboratory printouts. In addition, all patient questionnaires (self-reporting) are also considered source data. Study data are to be recorded from patient files.

### Patient Identification

All patient data are pseudonymized. Each patient will be clearly identified by a patient identification number assigned at each study center. The investigator will keep a patient identification list documenting the patient identification number with the patient’s full name, date of birth, sex, and date of informed consent.

The patient identification list is part of the investigator file and will remain at the clinic. The patient identification number consists of a 2-digit clinic number, a hyphen, and a running 3-digit number of recruited patients per study center.

### Trial

#### Start of Patient Participation

Any patient with a clinically and endoscopically confirmed diagnosis of UC and qualified for golimumab treatment according to routine medical practice is a potential study candidate. All potential candidates who come to the attention of the investigator will be informed regarding the possibility of participating in the study. Potential candidates interested in participating in the study will be promptly informed about the study in order to obtain their informed consent in accordance with the section “Patient Information and Informed Consent”.

#### End of Patient Participation

The observation of each patient ends according to the schedule with the last study visit. A patient’s participation in the study will be terminated prematurely if at least one of the following criteria is met: (1) withdrawal of informed consent, (2) termination of golimumab treatment, (3) lack of medical justification for further participation in the study, (4) premature termination of the complete trial, or (5) subsequent discovery that not all inclusion criteria are met and/or that any exclusion criteria are met.

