### Study Population

The evaluation of primary and secondary outcomes is carried out according to the intention-to-treat principle. The corresponding population comprises all patients included in the study regardless of possible protocol violations (eg, dropouts). In addition to intention-to-treat analysis, sensitivity analysis according to the per-protocol principle is carried out. Relevant protocol violations leading to exclusion from the per-protocol group are defined in the statistical analysis plan.

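### An undefined exit rule can end recording for eligible patients still on golimumab before Week 26, and with no imputation their outcome is lost to the primary model

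*Protocol article*

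**What the plan says.** The section End of Patient Participation lists five criteria. They are mandatory and any one suffices: "participation in the study will be terminated prematurely if at least one of the following criteria is met". The third is "lack of medical justification for further participation in the study". The others are withdrawal of consent, "2) termination of golimumab treatment", termination of the whole trial, and later discovery of ineligibility.

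Participation itself is described as follows. Study-Specific Interventions: "No medical interventions are carried out in the course of the study other than those required by standard medical procedure". Schedule of Visits: "the only clinical and laboratory data recorded are those corresponding to standard medical procedure". The one addition is that on routine blood samples "golimumab serum levels and ATG levels should also be monitored if possible". After baseline, these levels are scheduled for Weeks 2 and 6 only. Justifications for Trial Design repeats that treatment and monitoring follow current practice and not a study protocol.

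On analysis, Study Population says of the intention-to-treat set: "The corresponding population comprises all patients included in the study regardless of possible protocol violations (eg, dropouts". The Analysis section rules out imputation and specifies a logistic regression for Week 26 response from Week 6 data.

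**The concern.** The third criterion can act on its own only where the other four do not apply, that is, for an eligible, consenting patient who is still receiving golimumab in a trial that is still running. This is the patient whose Week 26 response the study needs. After Week 6 the study asks nothing of that patient beyond entries from routine care, so it is unclear what medical justification could lapse.

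The exit can occur once the Week 6 calprotectin change and the clinical course are known. Keeping the patient in the intention-to-treat population does not help, because without imputation a patient with no Week 26 outcome contributes nothing to the regression. A statistical analysis plan cannot recover an outcome that was never recorded.

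At stake is mainly the study's stated aim, a calculated probability of Week 26 response. If exits follow clinical course, those probabilities are estimated in a selected group. The primary coefficient is at risk under a further condition, set out in the working.

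**Working it through.** **Inputs.** From Sample Size: 80% of patients with calprotectin decline, 40% response, odds ratio (OR) 10, 58 evaluable, 61 recruited, 5% excluded. From Analysis: two-sided alpha 0.05, 80% power, no imputation. The number of exits under the third criterion is not given, so all removals below are assumptions.

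**The plan's own figure.** A likelihood-ratio power calculation for one binary predictor with prevalence 0.80, reading 40% as the response probability at the predictor mean, gives 57.7, so 58. The same method reproduces all nine evaluable numbers in Table 3. 58 × 1.05 = 60.9, so 61. The sample size is not in question here. The plan leaves room for 61 − 58 = 3 losses (3/61 = 4.9%).

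**Planning cells.** Reading 40% as the overall rate in 58 patients, OR 10 implies response of 47.9% with decline and 8.4% without. Rounded to whole patients:

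- with decline: 22 responders, 24 non-responders (46)
- without decline: 1 responder, 11 non-responders (12)

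OR = (22 × 11)/(24 × 1) = 10.1; likelihood-ratio p = 0.007; overall response 23/58 = 39.7%.

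**Removing non-responders from these cells.**

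| Non-responders removed (assumed) | OR | LR p | Response, decline | Response, no decline |
|---|---|---|---|---|
| none | 242/24 = 10.1 | 0.007 | 22/46 = 47.8% | 1/12 = 8.3% |
| 3 without decline | (22 × 8)/24 = 7.3 | 0.028 | 22/46 = 47.8% | 1/9 = 11.1% |
| 5 without decline | (22 × 6)/24 = 5.5 | 0.077 | 22/46 = 47.8% | 1/7 = 14.3% |
| 5 with decline | (22 × 11)/19 = 12.7 | 0.003 | 22/41 = 53.7% | 1/12 = 8.3% |
| 2 with, 1 without | (22 × 10)/22 = 10.0 | 0.008 | 22/44 = 50.0% | 1/11 = 9.1% |

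**General rule.** Let s1 and s0 be the fractions of non-responders retained with and without decline, with all responders retained. The observed OR is the true OR × s0/s1. It is unchanged when s0 = s1. The observed response probability in a group with true probability p is p/(p + (1 − p)s), which exceeds p whenever s < 1.

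Using the probabilities that reproduce the plan's 58 (51.4% with decline, 9.6% without, 43.0% overall) and 61 recruited:

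- Equal loss of 10%, 20% or 30% of non-responders: evaluable N is 57.5, 54.0 or 50.6; response given decline is 54.0%, 56.9% or 60.2% instead of 51.4%; OR stays 10; power is about 80%, 78% or 76%.
- Loss of 10% of non-responders with decline and 40% without: OR = 10 × 0.6/0.9 = 6.7; N = 54.2; power is about 56%.

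**The case against.** A reader might infer that the treating physician decides, and that the clause will take out patients who are doing badly. The document supports neither. It names no decision-maker, and the words could equally cover patients doing well, a transfer of care or an intercurrent illness. That objection stands. What remains is that an undefined exit, available once the predictor may be known, permits selection in either direction.

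A reader might also infer that the odds ratio must be biased, or that significance would be lost. That does not follow either. The larger shifts come from placing every removal in one cell. Five of the 11 non-responders without decline is 45% of that cell, and 5 of 58 (8.6%) exceeds the whole 5% allowance. A roughly proportional removal of three leaves the OR at 10.0.

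The golimumab-stopping criterion in the same list is the more explicit outcome-related exit, since the Introduction says that poor response after Week 12 often leads to discontinuation. This is correct, and it means that deleting the third criterion alone would not secure Week 26 outcomes.

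Participation is not purely documentation, because drug and antibody levels are added in Weeks 2 and 6. This is true, but it gives the clause no purpose after Week 6.

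Finally, this is a condensed article, and the full protocol may define the term. If so, the sponsor can cite the definition. The article nevertheless states the rule as mandatory, and it governs whether data are collected at all, which goes beyond a detail left to the analysis plan.

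**Conclusion.** The point holds in a limited form. The third criterion is a mandatory, undefined, stand-alone exit that fits poorly with a study recording routine care, and without imputation each exit before Week 26 removes an outcome from the primary model while the patient stays nominally in the analysis population.

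If exits depend on clinical course, the predicted probabilities are biased. With equal loss of 10% to 30% of non-responders, response given decline is overstated by about 3 to 9 percentage points (51.4% to between 54.0% and 60.2%). The odds ratio is biased only if exits also depend on calprotectin, and the direction is then open: 7.3 or 12.7 against 10.1 in the illustrations. No expected effect can be given, because usage is unknown. The illustrations also assume that only non-responders are lost and reduce the primary model to a two-by-two table. The planned sample size is unaffected.

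**What to change.** In End of Patient Participation, delete the third criterion as a reason to end documentation. State that eligible patients who have not withdrawn consent remain under routine-care documentation, including the partial Mayo score, to Week 26. Reconcile the golimumab-stopping criterion with this rule, so that stopping the drug does not by itself end data recording.

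This concerns data recording only and changes no treatment decision. The cost is a short edit to one section and a few more routine-care entries. The partial Mayo score at Week 26 is already on the documentation schedule, so no new procedure is needed.

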#### Trial Duration/End of Trial

The recruiting phase has a planned duration of 18 months. The observational phase has a planned duration of 26 weeks. The complete trial is considered to have ended after all queries from the study coordination center have been answered by each individual study center, but at the latest 4 months after the last visit of the last patient.

Study centers that grossly violate the AMG, data protection regulations, or the GCP guidelines can be excluded from the further recruitment and observation of study patients. Premature termination of the study as a whole will be taken into consideration if ethical or scientific justification for the trial is compromised or no longer valid, errors or violations significantly compromise the scientific integrity of the data collected for the study with regard to the study aims, or the requirements for a successful execution of the study are no longer fulfilled for other reasons.

The principal investigator will consult the corresponding biometrician regarding any possible premature termination of the trial. The minutes of the aforementioned consultation meeting will be recorded and subjected to the approval of both parties. Any decision regarding the premature termination of the trial will be taken jointly by the principal investigator and the corresponding biometrician.

### Data Quality Assurance

Upon receipt at the study coordination center, CRF will be checked for completeness and consistency (in-house review). Queries will be generated for missing or implausible entries and sent to the corresponding study centers. After the clarification of implausible entries and completion of missing data, CRF will be handed over to the corresponding data management department for data entry.

### Quality Control and Assurance

Quality control in the study is ensured by the possibility of monitoring the study centers involved. For each monitoring visit, a monitoring report is generated documenting the progress of the observational study and describing any problems that may have arisen. The exact nature and extent of the monitoring activities are described in a separate monitoring manual. All investigators declare their consent to regular visits of study monitors to the study centers. In addition, they must provide direct access to all necessary study documents, including original patient documents relevant to the study. The principal investigator and/or auditors designated by the principal investigator are entitled to conduct audits at the study centers and any other facilities participating in the study. They are entitled to inspect and review all study-relevant documents. This right also applies to regulatory inspectors.

### Ethical and Regulatory Aspects

The study is conducted in compliance with the current version of the Declaration of Helsinki (10/2013, Fortaleza, Brazil). This study cannot begin before approval has been obtained from the corresponding ethics committee. Prior to inclusion in the study, the investigator will inform each patient about the nature, significance, risks, and scope of the study, as well as the patient’s right to withdraw from the study at any time without prejudice. An informed consent form is handed to the patient describing the study in non-scientific and generally understandable language. Each patient must consent to study participation in writing. The patient must be provided with ample time to make a decision and given the opportunity to ask any questions before the consent form is signed. In accordance with AMG, § 40 Abs. 2a, patients are informed that the data related to their disease will be stored with a pseudonym and analyzed for scientific purposes. Patients must consent to the use of their pseudonymized data in writing. Informed consent forms are to be signed and dated by the patient and the treating physician.

This clinical study is carried out in conformity with the requirements of the current German Medicinal Products Act, as well as all applicable legal provisions regarding data protection and the GCP guidelines. The general notification requirement as per § 67 AMG will be complied with.

## Results

Enrollment started in October 2014 and was still open at the date of submission. The study is expected to finish in December 2016.

## Discussion

### Rationale for the Trial

The early identification of patients who are responding well to an anti-TNFα-antibody is therapeutically beneficial. At the same time, patients who are not responding can be identified earlier. The development of a therapeutic algorithm for identifying patients as responders or non-responders can help prescribing physicians both to avoid ineffective treatments and to adjust dosages when necessary. This in turn would promote a higher degree of treatment tolerance and patient safety in the case of anti-TNFα antibody administration.

There is a clear association between detectable trough levels of anti-TNFα inhibitors and clinical therapeutic response. On the other hand, the detection of anti-drug antibodies is associated with a poor response.

Fecal calprotectin levels reflect mucosal inflammation status. The strong correlation between high fecal calprotectin and mucosal inflammation has been widely described. Furthermore, it is also clear that fecal calprotectin levels decrease if there is therapeutic response.

A regular question among IBD patients is how long they will have to take their medication in total. Yet there is currently insufficient data regarding optimal treatment length with TNFα inhibitors. In view of the elevated costs and possible side effects associated with this type of treatment, it is desirable to clearly define a patient population for which continued therapy is justifiable.

### Justifications for Trial Design

This study is prospective, as the aim is to use the data from trial Week 6 to calculate the probability of clinical response in Week 26. Only one study cohort is required to answer this question, and no comparison group is necessary.

In order to achieve a higher degree of representativeness of the results for the intended population, the trial is carried out throughout Germany and at multiple centers specifically chosen for this purpose. Treatment, including diagnosis and monitoring, does not follow a predefined study protocol and is carried out exclusively in accordance with current medical practices. The aim of this non-interventional approach is to ensure a high degree of representativeness of the study results for daily medical practice.

### Conclusion

This early Monitoring of Response (MORE) study aims to achieve a more thorough understanding of therapeutic development in patients with moderate to severe ulcerative colitis receiving regular doses of golimumab by developing an algorithm for optimizing golimumab administration in patients with moderate to severe ulcerative colitis.

## Abbreviations

AMG: Arzneimittelgesetz, German Medicinal Products Act
ATG: antibody towards golimumab
CRF: case report form
CRP: C-reactive protein
DRKS: Deutsches Register Klinischer Studien, German Clinical Trials Register
GCP: good clinical practice
GLM: golimumab
IBD: inflammatory bowel disease
ICH: International Conference on Harmonization of Technical Requirements for Registration of Pharmaceuticals for Human Use
OR: odds ratio
TNFα: tumor necrosis factor alpha
UC: ulcerative colitis
WBC: white blood cells
